## Methods/Design

### Procedures

For this study, we propose to develop and test a brief mobile (i.e., mobile phone-friendly website) intervention directly targeting pregaming among college students. First, we developed the intervention content and programmed the online intervention. We then beta-tested the developed program with heavy drinking college students who reported pregaming at least once per week on average and gathered feedback regarding feasibility and acceptability of intervention content. Final edits to the brief intervention were made based on these students’ feedback. Next, we will conduct a randomized controlled trial (RCT) of the intervention with approximately 500 college students from one private southern California university, assigning half to intervention and half to control. We will evaluate immediate term (from two weeks pre-intervention to two weeks post-intervention) and short term (from one month pre-intervention to six weeks and 14 weeks post-intervention) drinking during pregaming, overall drinking, and consequences.

For the RCT, we will recruit (1) full time undergraduate students at the university who are (2) between the ages of 18 and 24 and (3) report pregaming at least once per week in the past month. No other eligibility criteria beyond these will use in an effort to obtain students who pregame but who may not be considering making changes to their drinking. Participants will be recruited by emails sent to a random selection of undergraduates, via a list of student emails obtained from the university’s registrar. Participants will complete a screening questionnaire to determine if they meet eligibility criteria. Those screening into the study will complete a 20-min baseline survey, followed by two weeks of daily surveys. Participants will then be randomized to receive the brief pregaming intervention or a control condition program (randomized by computer-generated random numbers). After viewing one or the other program, they will complete two additional weeks of daily surveys, followed by a 20-min one-month follow-up survey (completed online six weeks post-intervention) and a final 20-min follow-up survey two months later (completed online 14-weeks post-intervention). See Fig. 1 for RCT study flow. Participants receive a $20 gift card (multiple options to choose from such as Amazon, clothing stores, and coffee shops) for each of the three 20-min surveys. For each of the 28 two-minute daily surveys they complete, participants will receive $2 added to a gift card balance, for a total of $56 if all daily surveys are completed. It is made clear to participants that incentives are provided for completing the surveys, not for completing the intervention (or the control condition). All procedures have been approved by the Institutional Review Board at the university where the research is being conducted.

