### Analytic plan

#### Main effects

Main effects of the intervention will be evaluated for pregaming drinking, general drinking (i.e., drinks consumed both during and after pregaming), and alcohol-related consequences in the immediate term and short-term. In the immediate term, we will evaluate whether intervention participants pregame less frequently (i.e., fewer days per week), reach lower BALs on pregaming days, and consume fewer drinks during pregaming from the two weeks prior to the intervention to the two weeks post-intervention than those in the control condition. Estimated BALs will be calculated using Widmark’s formula, which is the standard method for estimating BAL (using sex, weight, amount consumed, time). We will also evaluate whether, compared to control, intervention participants drink fewer days overall (i.e., pregaming days and non-pregaming days), consume fewer drinks over the course of each drinking day, and report fewer consequences on drinking days from the two weeks prior to the intervention to the two weeks post-intervention. In the short term (baseline to six and 14-weeks post-intervention), we will evaluate main effects of the intervention on pregaming frequency (i.e., pregaming days in the past 30 days) and pregaming quantity (i.e., typical amount consumed during pregaming on pregaming days in the past 30 days). We will also evaluate main effects of the intervention on overall drinking days (i.e., pregaming days and non-pregaming days) in the past 30 days, average consumed on a typical drinking day in the past 30 days, and number of alcohol-related consequences experienced in the past 30 days.

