#### Baseline and follow-up surveys

On the screening questionnaire, participants will be asked, “During the past 30 days, how often did you engage in pregaming,” with response options of never, just once, a couple of times, about once per week, a couple of times per week, and daily or almost daily. Those endorsing about once per week or more will screen into the study and complete the baseline survey. Overall drinking frequency will be assessed with an item asking, “During the past 30 days, how many days did you have at least one drink of any alcoholic beverage, such as beer, wine, hard seltzer, mixed drinks, or shots of liquor,” with response options from 0 to 30 days. To assess overall drinking quantity, participants will then be asked to consider their typical drinking behavior over the past 30 days with, “During the past 30 days, on the days when you drank, about how many drinks did you drink on average,” with response options from 0 to 30 drinks. Pregaming frequency will then be asked with the item, “During the past 30 days, how many days did you engage in pregaming,” with response options from 0 to 30 days. Pregaming quantity will be assessed with an item asking, “During the past 30 days, on the days when you drank, about how many drinks did you drink during pregaming,” with response options from 0 to 30 drinks. Alcohol consequences will be assessed with the Brief Young Adult Alcohol Consequences Questionnaire (B-YAACQ) [84, 85], where participants will indicate which (yes/no) of 24 alcohol-related consequences have happened to them in the past 30 days (e.g., I drove a car when I knew I had too much to drink to drive safely, I did not remember large stretches of time while drinking heavily). Participants will indicate race/ethnicity and class year (for descriptive purposes), age and biological sex (for moderation analyses), weight (for calculating estimated BAL), complete the 10-item AUDIT [76] (for moderation analyses), and indicate how motivated they are to drink less using a change ruler (scale from 0–10) modified from other work [86, 87] (for moderation analyses). Follow-up surveys will also ask intervention and control participants how long they spent viewing the content and whether they returned to review the content after initial viewing. Back-end data connected to PIN codes can also be used to determine whether participants finished viewing the intervention or control content or only completed a portion of either.

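### The short-term baseline ends about two weeks before the intervention and overlaps the screening window; reword it, adjust also for the pre-randomisation diary, and rest conclusions on the between-arm contrast

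*Protocol article*

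**What the plan says.** The Procedures section defines the later evaluation as "short term (from one month pre-intervention to six weeks and 14 weeks post-intervention". The Main effects section of the analytic plan names the same starting point only as baseline: "In the short term (baseline to six and 14-weeks post-intervention), we will evaluate main effects of the intervention on pregaming frequency".

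Procedures also gives the order of events. "Those screening into the study will complete a 20-min baseline survey, followed by two weeks of daily surveys", and after those daily surveys "Participants will then be randomized to receive the brief pregaming intervention or a control condition program".

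The baseline and follow-up outcome items use a 30-day recall, for example "During the past 30 days, how many days did you engage in pregaming". Entry to the trial uses a separate ordinal item with the same recall, "During the past 30 days, how often did you engage in pregaming", and "Those endorsing about once per week or more will screen into the study and complete the baseline survey". This applies the criterion that students "report pregaming at least once per week in the past month".

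Main effects links the two pre-intervention diary weeks to the immediate-term outcomes. It does not mention them for the six- and 14-week outcomes.

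**The concern.** The sentence in Procedures sets two windows side by side. The immediate-term window starts two weeks before the intervention and means the 14 days that end there. A reader will take the matching one-month phrase in the same way, as the 30 days ending at the intervention. The schedule does not deliver that window.

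In addition, students enter because they report frequent pregaming over a 30-day period that the baseline survey then largely measures again. A measurement taken in the window used for selection tends to be high, and later measurements tend to fall back. If results are described as movement from baseline to follow-up, part of that movement is regression to the mean. The limitations section offers self-monitoring as a reason why controls may change but does not mention selection. A fall in either arm could therefore be credited to the wrong cause.

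The trial also holds a measurement taken after selection, before randomisation and nearer to the intervention. The article puts it to use only for the immediate term.

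**Working it through.** The plan gives no figure to reproduce here. The check is calendar arithmetic, followed by simulation under assumed distributions, because the document gives no distribution for pregaming days.

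**1. Window.** Let day 0 be the intervention. With 14 diary days directly before it, the baseline survey falls on day -14. Its recall runs from -14 - 30 = -44 to -14 - 1 = -15. The month before the intervention is day -30 to -1. The shared days are -30 to -15, which is 16 of 30, and the last 14 are missed. With a 7-day gap between the survey and the first diary day, the recall runs from -51 to -22 and shares 9 of 30. The document states no gap.

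**2. Overlap with selection.** Screening and the baseline survey both ask about the past 30 days. No interval between them is stated. If they are done close together, the two windows are nearly the same.

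**3. Direction and size of the fall with no treatment effect.** Two simulations with different assumptions agree on direction.
- *Gamma-Poisson counts:* unselected mean 3.5 days, SD of person rates 3.0, correlation between windows 0.40 to 0.62, entry at 4 or more days in 30, n = 500 allocated 1:1, 1,000 replicates. The selected baseline averages 7.3 to 8.3 days, against 5.7 to 5.9 in the control arm at follow-up. The fall is 1.3 to 2.6 days.
- *Weekly binomial counts with drifting person rates:* mean 0.12 to 0.15 pregaming days per day, between-student CV 0.5 to 0.7, weekly autocorrelation 0.7 to 0.97, entry at 4 or more days in four weeks. The baseline is about 6.1 days and the next two weeks run at 4.9 to 5.1 per 28 days, a fall of about 16% to 19%.

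Both select on the baseline count itself, which is the strongest form of the artefact.

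**4. Effect on the randomised comparison.** In the gamma-Poisson simulation the baseline-adjusted difference between arms was -0.01 to +0.01 days and the type I error 3.9% to 5.3%. Replacing the selected baseline by a fresh one changed the standard error by only about 1% to 2%.

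**5. Gain from adding the diary to the survey value.** This is a different question from step 4. The reduction in residual variance is 1 - (1 - R² with both) / (1 - R² with survey alone). The four scenarios of the binomial simulation give:

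| Time | R² survey alone → both | Reduction |
|---|---|---|
| 6 weeks | 0.20 → 0.28 | 1 - 0.72/0.80 = 10% |
| 6 weeks | 0.15 → 0.22 | 1 - 0.78/0.85 = 8% |
| 6 weeks | 0.30 → 0.38 | 1 - 0.62/0.70 = 11% |
| 6 weeks | 0.11 → 0.16 | 1 - 0.84/0.89 = 6% |
| 14 weeks | 0.15 → 0.19 | 1 - 0.81/0.85 = 5% |
| 14 weeks | 0.12 → 0.16 | 1 - 0.84/0.88 = 5% |
| 14 weeks | 0.24 → 0.30 | 1 - 0.70/0.76 = 8% |
| 14 weeks | 0.10 → 0.13 | 1 - 0.87/0.90 = 3% (about 4% before R² was rounded) |

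A further simulation, with entry decided either exactly or with noise, gave about 7% to 14% at six weeks and 4% to 10% at 14 weeks. In it the diary predicted follow-up roughly as well as the survey did. The overall range is 4% to 14%. On the scale of the standard error, 1 - √0.96 = 2% and 1 - √0.86 = 7%.

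**The case against.** The strongest reply is that nothing in the planned inference is wrong. The one-month phrase is a summary. It can be read as a month-long recall taken before the intervention, or as roughly a month before it, since the midpoint of the window is day -29.5. Main effects says only baseline, and the order of events is stated openly. This stands in part: the wording is loose, not a firm contradiction, and correcting it alone would be clerical.

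A reader might infer that the treatment effect is biased. The documents do not support that. Selection comes before random allocation, so regression to the mean is equal in expectation in both arms, and the article plans comparisons against control.

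A reader might also infer that every short-term baseline is inflated. Selection acts directly on pregaming frequency only, through an ordinal item separate from the baseline count. Quantity, overall drinking and consequences are affected indirectly, and the size of any inflation cannot be computed from the document.

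It is tempting to show the diary weeks as the level that reveals the selection drop. That fails. The limitations section allows that repeated self-reporting may itself reduce drinking, and daily report differs from 30-day recall as an instrument. The diary level would mix all three influences.

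Finally, covariates may be settled in an analysis plan that is not shown, and diaries may be incomplete because students are paid per survey completed. Both points stand. The covariate is therefore a recommendation and not a claimed omission, and it needs a rule for missing values. Neither reactivity nor the change of instrument biases an adjustment for a value measured before randomisation.

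**Conclusion.** The point holds at low severity. The short-term baseline covers about day -44 to -15 if the steps follow one another without gaps, and it largely overlaps the screening window if screening and baseline are close together. A fall in pregaming frequency should then be expected in both arms with no effect. Its direction is secure, but its size rests on assumed distributions. The between-arm estimate is unbiased; only a within-arm reading of change is at risk.

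The useful gain is in precision. Adjusting for the diary as well as the survey lowers residual variance by about 4% to 14%, or roughly 2% to 7% of the standard error. For 500 students that is worth about 500/0.96 = 521 to 500/0.86 = 581 students adjusted for the survey alone. These figures concern pregaming days and assume complete diaries and follow-up, so the real gain may be smaller.

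**What to change.** 1. In Procedures, describe the short-term baseline as the 30 days before the baseline survey, ending about two weeks before the intervention.
2. In the six- and 14-week models, adjust for the pre-randomisation diary value as well as the baseline survey value, at least for pregaming days and drinking days. Fix a simple rule in advance, blind to arm. For example, use the rate over completed diary days, with a mean value and an indicator when the diary is empty. If pregaming quantity is included, use the same device for students with no pregaming day in those two weeks.
3. State that conclusions rest on the between-arm contrast, and that a fall from baseline within an arm is not evidence of response.

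The cost is one corrected sentence, one extra covariate per model and some handling of missing diary values. No new data are needed and participants carry no added burden.

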**Fig. 1 Fig1:**
[figure not shown]
Flow of the RCT

### Development of the intervention

#### Overview

The intervention, called Pregaming Awareness in College Environments (PACE), is comprised of a theoretically-informed, brief, accessible, and personalized intervention to address pregaming drinking among college students that is based on empirically-supported intervention components. It is tailored toward an individual’s personal goals, beliefs (perceptions, expectancies, self-efficacy), and behavior (protective strategies), focusing on the core components of brief interventions that mediate the effects of multiple component intervention programs (e.g., correcting perceived norms, use of protective behavioral strategies, increased self-efficacy, challenging expectancies, BAL feedback) [17, 18]. Content was informed by the BASICS approach [61], which is based on aspects of both Motivational Interviewing [62] and relapse prevention [63] and rooted in a harm reduction framework [15, 16]. BASICS for general drinking has been efficacious when delivered in individual and group formats [64, 65] and recently has been adapted for use on mobile phones [66]. Researchers found in a study of 94 heavy drinking college students that components of the BASICS intervention in a mobile format led to limited drinking during the 14 days of the study [66]. Yet, the intervention failed to demonstrate one-month effects on heavy drinking behavior compared to control. It is possible that minimal lasting effects were found after the intervention ended due to lengthy, non-targeted content (e.g., participants received a mean of 23 modules, 3–5 min each, with additional focus on smoking cessation). The innovation in the PACE intervention comes from its targeting of pregaming behavior directly, with components of BASICS modified to address this risky drinking practice. PACE presents videos with a female narrator, combined with interactive activities to engage participants and help them consider making changes to their pregaming behavior.

#### Format of the intervention

Nearly all college students own and use smartphones regularly [67]. Young adults report checking these phones constantly throughout the day at an average of 74 times per day [68]. Moreover, alcohol interventions based on BASICS components that are delivered online through computers, tablets, or mobile phones have shown efficacy and are a means to reach individuals with intervention efforts that may not have otherwise sought in-person care [69, 70]. Thus, we opted to deliver PACE to participants on mobile phones and created a mobile-friendly website to host the program. Students could log in and view the program, which takes an average of 25 min to complete. The mobile format increases access to the intervention, without need for in-person facilitator delivery or use of a desktop or laptop computer.

#### Intervention content

PACE begins with definitions and activities to help students better understand standard drinks (e.g., 12 oz of beer or one shot of most liquors), BAL, and alcohol metabolism rates. Students learn that alcohol takes time to be processed; thus, when consuming many drinks in a short period of time, this can place them at higher than anticipated levels of intoxication once arriving at the event. Often students do not feel the full effects of pregaming until they arrive at their destination [39, 44]. Participants receive BAL feedback and learn about alcohol’s biphasic curve and the point of diminishing returns (BAL of 0.05–0.06), where the “good things” about alcohol (e.g., feel relaxed and social) are maximized and there is *less* (not no) likelihood of experiencing the “not so good things” (e.g., consequences). This is important as students reach high BALs even before leaving for the night out; as BALs rise, potential for consequences increases [35, 49].

Students then learn that students at their school pregame less frequently and drink significantly less during pregaming than they perceived. Research shows that students have misperceptions of pregaming perceived norms and such misperceptions associate with their own pregaming drinking behavior [71]. Prior work has shown that reductions in perceived norms are one of the driving components of change in brief interventions with students, [18] and that reductions in tailgating norms (i.e., tailgating being one of the many contexts where pregaming occurs), specifically, mediated changes observed in a tailgating-focused brief intervention with students during a football game on campus [60]. Thus, during PACE, students are asked about the typical pregaming behavior (frequency in past 30 days, amount consumed per pregaming occasion) of their peers on campus, as well as how much they drink themselves. Graphs with descriptions, narration, and the source of the norms are presented on screen, with content showing the discrepancies between one’s own perceptions and actual norms, as well as between one’s own use and actual norms. Students see pregaming norms for both males and females on campus. This is followed by a video describing the theory behind how social norms work to perpetuate heavy drinking in college [72]. Campus norms were collected in the spring of 2019 in a first phase of the study, among 527 students from the university recruited through a random list from the university registrar. This sample was similar in demographics to the larger university community (mean age 20; 62% female, 56% racial/ethnic minority students), with 69% reporting pregaming behavior. Details about the Phase 1 norms documentation can be found elsewhere [73].

PACE content also focused on goals for the night (i.e., reasons for pregaming) and students learn that they can get what they want out of the night (e.g., feel relaxed, be more social) by drinking moderately or not at all during pregaming. Relatedly, participant’s pregaming-specific expectancies and beliefs that pregaming will make their night better are challenged through a presentation on alcohol placebo studies, where students hear about experiments where college students display the social effects of drinking even without consuming actual alcohol. This is important because students with positive outcome expectancies (e.g., it would be easier to talk to people) are more likely to pregame, and pregaming mediates the relationship between expectancies and hazardous drinking [74]. Participant’s drink refusal skills are reviewed with alternate strategies to use if feeling pressured to drink heavily during pregaming, as greater drink refusal self-efficacy associates with less pregaming [75]. As in a relapse prevention approach, which targets the people, situations, and feelings that may lead one to drink heavily [63], risky situations specific to the students (e.g., when in a large group, when getting ready to meet a potential romantic partner later that night) are reviewed. Protective drinking strategies specific to pregaming [73] are selected by the students and they are asked to try during their next pregaming event strategies they do not normally use.

The intervention concludes with a video summarizing the content and a personalized feedback sheet with resources, that also gets emailed to participants. The personalized feedback sheet contains the information from the intervention in a format viewable at a later time, as well as resources for seeking help on campus and in the community for drinking, sexual violence, and mental health.

### Beta test of the intervention

Participants completing the norms documentation survey were asked at the end of the survey if they would be interested in attending a focus group to offer feedback on the intervention once it was completed. Of the 527 participants, 75 met eligibility criteria and expressed interest in attending a focus group. In August 2020, we invited these 75 participants and obtained consent from 13 of them to review the first draft of the PACE intervention and provide feedback. These participants attended one of three online focus groups to provide feedback to our research team on what they liked and did not like, what could be improved regarding content and functionality, and ideas for improving engagement with the program. Focus groups were conducted online rather than in person as initially proposed, due to COVID-19 pandemic safety protocols. Focus group participants were provided with a $50 Amazon gift card.

Focus group participants’ feedback was primarily positive and generally focused on what they liked about the PACE intervention. Still, we prodded students to generate suggestions for improvement. Feedback that could feasibly be addressed within the scope of the budget was incorporated in the intervention and prepared for a final version to test in the RCT. Suggestions included modifying the graphs displaying the normative drinking patterns to improve readability, adding brief text introductions to each section to facilitate fluidity between sections, modifying images used for standard drinks (including adding an image of sake), adding additional protective strategies (e.g., avoiding use of motorized scooters after pregaming), correcting a few typos and modifying some color schemes, and adding additional campus-specific resources to the resources page.

